## 5.6 Randomization Codes

This study will be double-blinded. Subjects will be randomized upon confirmation of eligibility to receive either active or placebo investigational product in a 1:1 ratio. A randomization schedule will be generated using the SAS® procedure PROC PLAN. This will be generated and filed in such a manner so as to ensure that all study personnel remain

blinded until such time as the database is locked and the study unblinded. Randomisation will be performed in block sizes of 4.

Subjects will be allocated a sequential randomization number. The number will consist of a 3 digit-sequential number pre-fixed by a 1-digit unique site identifier.

## 6 METHODS

### 6.1 Inclusion Criteria

1. Male and female volunteers aged 18-45 years (inclusive)
2. Anti-Tat antibody negative
3. HIV-1 infected individuals currently receiving treatment with ARVs
4. Chronically suppressed HIV-1 infection as indicated by a HIV-1 plasma viraemia < 400 copies/ml and a CD4+ T cell count  $\geq$  200 cells/ $\mu$ l at screening, and documented at least once during the 12 month period prior to screening, irrespective of the pre-ARV CD4 nadir.
5. Negative pregnancy test for females of childbearing potential (not sterilized and still menstruating or within 1 year of the last menses) to be performed during the screening phase and immediately before each vaccination, and use of an acceptable method of contraception (double barrier methods, combined oral contraceptives, injectable contraceptives or intra-uterine devices) for at least 3 weeks prior to the first vaccination and for the duration of the study
6. Has provided written informed consent.
7. Agrees to stay in contact with the research site for the duration of the study

### 6.2 Exclusion Criteria

1. Acute illness on Study Day 0
2. Body temperature  $\geq 37.5$  °C on Study Day 0
3. Any current AIDS-related opportunistic disease
22. Any current neoplastic disease [*NOTE: Criterion is meant to exclude volunteers with active invasive cancer. Volunteers who present with intraepithelial neoplasia during the course of the study are to continue with all study procedures.*]
4. Known history of malignant neoplastic diseases [*NOTE: Subjects with known history of non-malignant neoplastic diseases that are completely resolved according to the fulfilment of all the specific recovery criteria, in agreement with the current guidelines in medical oncology, are eligible*]
5. Known history of encephalopathy, neuropathy or unstable CNS pathology, immunodeficiency, autoimmune disease, angina or cardiac arrhythmias, or any other clinically significant medical problems in the opinion of the investigator
6. Any evidence, as judged by the investigator, of unstable cardio-vascular disease (e.g. unstable hypertensive disease needing modification or introduction of an anti-hypertensive treatment)

7. Chest radiography showing evidence of active or acute cardiac or pulmonary disease within 6 months prior to the study screening visit [Note if no previous chest X-ray available, this will be performed at screening];
8. Known history of anaphylaxis or serious adverse reactions to vaccines
9. Known history of serious allergic reaction to any substance, requiring hospitalization or emergent medical care (e.g. Steven-Johnson syndrome, bronchospasm, or hypotension)
10. Active pulmonary tuberculosis within 12 months of screening as evidenced by chest radiography and/or medical history.
11. Any known medical or psychiatric condition which precludes subject compliance with the protocol, specifically, persons with psychotic disorders, major affective disorders and/or suicidal ideation are to be excluded
12. Current use of psychotropic drugs prescribed for major psychotic disorders
13. Concomitant participation in any study with an investigational product or device
14. Current or prior therapy with immunomodulator, immunosuppressive and/or anticoagulant drugs within 30 days prior to administration of the investigational product
15. Live attenuated vaccines within 60 days of the first administration of the investigational product [*NOTE: Medically indicated sub-unit or killed vaccines (e.g., influenza, pneumococcal, hepatitis A and B) are permitted, but must have been administered at least 4 weeks prior to the first administration of the investigational product*]
16. Known receipt of blood products or immunoglobulins during the year prior to screening
17. Previous participation in an HIV-1 vaccine trial (subjects who are known to have previously participated in the placebo arm of an HIV-1 vaccine trial, and so have never received an investigational HIV-1 vaccine, are eligible for inclusion)
18. Known drug and/or alcohol abuse in the year prior to screening
19. Use in the last 6 months or concomitant use of anti-CCR5 inhibitors and/or integrase inhibitors and/or fusion inhibitors
20. Pregnant or lactating females

### 6.3 Screening Failures

The investigator will maintain a log of all screening failures. A screening failure is defined as any subject who signs the informed consent form but who does not meet the inclusion/exclusion criteria and is thus not randomized to receive the investigational product.

### 6.4 Randomization

*Volunteers will be allocated a screening number at the time of screening. This number will comprise the clinical trial code (T3) + a 2-digit site identifier (e.g. '01') + a 3-digit sequential recruitment number. For example, the first subject screened at clinical site number 01 would be assigned the screening code T301001, the second subject screened would be T301002 and so on. All screened volunteers will be assigned a screening number, irrespective of whether or not they will be included in the study. Once allocated, screening*

*numbers will not be re-used. The screening number will be used as the main subject identifier throughout the whole study.*

At the time of enrolment, subjects will be randomly assigned to a treatment regime in accordance with the randomization schedule. The site will allocate the next available sequential treatment number to each subject as they are randomized. Treatments will be allocated in balanced block-sizes of four. Allocation of the treatment number to a particular subject will only occur after confirmation of eligibility immediately prior to the first vaccination.

The original randomization list will be kept by Triclinium. A copy will be supplied to the GMP manufacturer in charge of the investigational product packaging and release.

## **6.5 Blinding/Un-blinding**

*Investigational product kits will be provided to the Investigators and their staff in a blinded fashion by the Sponsor. All clinical and laboratory staff and the subject will be blinded to treatment assignment (active treatment or placebo). Double-blinding will reduce the potential for observer bias and subject reporting bias.*

*Un-blinding will only occur at the end of the study after database lock or in the event of an emergency where knowledge of the treatment allocation is required for proper clinical management of the subject. If possible, sponsor approval should be sought prior to any emergency un-blinding procedure. In the interests of time, however, this may not be possible. The investigational site will be provided with randomization code envelopes together with the treatment kits. In the event of an emergency un-blinding, the investigator will record the reason for, and the date and time of the un-blinding in the source documents, the envelope and in the CRF.*

*The sponsor and CRO will be informed immediately of any emergency un-blinding that occurs at the site. This information will be communicated to the DSMB and will be detailed in the Clinical Study Report.*

## **6.6 Study Assessments**

The following section provides a detailed listing of the clinical, immunological and virological assessments to be performed during this study.

### **6.6.1 Clinical Assessments**

All clinical assessments will be performed at the clinical site; special investigations e.g. chest X-ray will be performed at the nearest referral centre.

### **6.6.2 Standard Laboratory Assessments**

The following laboratory assessments will be performed at the time points described beneath in section 6.7

#### **Haematology:**

Red cell count, haemoglobin, haematocrit, MCV, platelets, white cell count and differential counts (neutrophils, lymphocytes, monocytes, eosinophils, basophils)

**Clinical chemistry:**

Sodium, Potassium, Calcium, Total Protein, Albumin, Total Bilirubin, Alkaline Phosphatase, AST, ALT, GGT, Urea, Creatinine, LDH, CPK, Thyroid function tests (T4 and TSH)

**Coagulation:**

Thrombin Time, Prothrombin Time, APTT

**General Immunological parameters:**

CD4+ T cell counts, HIV-1/2 ELISA determinations

**Urinalysis:**

Dipstick determination of Protein, Glucose, Nitrites, Albumin, Leukocytes and Red blood cells

**Pregnancy test for females:**

Serum  $\beta$ HCG will be conducted at screening for all females; urine pregnancy test to be performed on all females of child-bearing potential immediately prior to each vaccination and at designated follow-up visits.

The total quantity of blood to be collected for the purposes of this study will be kept to the minimum volume (about 460 ml) that will facilitate the assessment of immunology and virology parameters as well as all the primary safety determinations necessary to fulfil the requirement for first line immunology and virology testing. Second line immunology and virology testing will be performed depending on the availability of residual specimens (PBMC, serum, plasma).

First line testing will include the minimal panel of assays required to identify the presence of an immune response to Tat, which represents the primary endpoint of the study. Second line testing is aimed at allowing a more detailed assessment of the immune response to Tat and for an in depth exploration of immunologic and virologic biomarkers of ARV efficacy and/or disease progression.

### **6.6.3 Immunological Evaluations**

Immunological evaluations will be performed according to “first line” and a “second line” laboratory testing by the designated Core Laboratory.

**First line immunology testing**

Assessment of anti-Tat humoral immune response:

- Determination of IgM, IgG and IgA anti-Tat antibodies in sera
- Titration of IgM, IgG and IgA anti-Tat antibodies

**Second line immunology testing**

The second line immunology testing will be performed retrospectively after the un-blinding, at the end of the study, on subgroups of participants defined on the basis of immunogenicity results.

In particular, lymphoproliferative responses (CFSE staining) or *in vitro*  $\gamma$ IFN, IL-4 and IL-2 production in response to Tat (ELISPOT) will be performed depending on the sample cell viability and recovery.

In addition, depending on the availability of residual specimens (PBMC, serum and plasma), the following tests will also be performed:

- Characterization of lymphocyte subsets (CD3, CD4, CD8, CD16, CD56, CD19)
- Anti-Tat IgG (IgG1, IgG2, IgG3, IgG4) subclasses
- Epitope mapping of IgM and IgG anti-Tat antibodies
- Neutralization of Tat activity by in vitro assays (rescue inhibition assay)
- Anti-HIV regulatory and structural proteins antibodies
- Antibody-mediated cellular cytotoxicity (ADCC)
- Inhibition of Tat uptake by MDDCs
- Neutralization of primary isolates (all clades)
- Anti-CCR5 antibodies
- Anti-CD4 antibodies
- Lymphoproliferative response to mitogens and recall antigens
- Lymphoproliferative response to HIV-1 Env (CFSE staining)
- *In vitro*  $\gamma$ IFN, IL-4 and IL-2 production in response to Env (ICS/Elispot)
- B cells phenotype (naïve and memory) and antigen specific antibodies
- Phenotype and functional characterization of regulatory T cells
- Intracellular PBMC staining for granzyme, perforin, cytokines and chemokines
- Analysis of Th1 and Th2 cytokines in sera and in PBMC supernatants
- Analysis of chemokines in sera and in PBMC supernatants
- Lymphocytes spontaneous cell death and PBMC cell viability
- B cell cloning
- Functional and molecular characterization of clono-specific antibodies
- Serum/plasma determination of soluble CD4
- Serum/plasma determination of phenotypic and biochemical markers of immune activation (CD38 expression, neopterin,  $\beta$ 2-microglobulin, C reactive protein, total immunoglobulin, sCD27, sCD14, LPS and IgM against endotoxin core antigen by ELISA)
- HLA typing.

#### 6.6.4 Virology Evaluations

Virology evaluations will be performed according to “first line” and a “second line” laboratory testing by the designated Laboratory to determine:

**First line virology testing** - HIV-1 plasma viraemia (viral RNA copies)

**Second line virology testing** - The following parameters will be determined, depending on the availability of residual specimens (PBMC, serum, plasma):

- HIV-1 sequencing and phylogenetic analysis
- HIV-1 Genotypic resistance
- HIV Viral tropism
- HIV-1 proviral DNA copies
- Assessment of co-infections (e.g. Syphilis, HBV, HCV, HHV8 and others)

Female participants only: Cervical swabs and Pap smears will be taken on 3 occasions during the course of the study in order to test for Human Papilloma Virus (HPV) infection.

Should any of the above co-infections be detected during the course of the study, participants will be referred to their healthcare provider for clinical management.

In addition, the assessment of antiretroviral drug concentration may be performed.

### 6.6.5 Sample Collection, Storage and Shipment

The volume of blood to be collected at each study visit will vary depending on the specific analyses to be performed at that visit. Approximate volumes for the assessments are 31 ml for immunology and virology evaluations and 19 ml for assessing safety parameters. The total volume that can be collected at any one visit is  $\pm 50$  ml as per the following table:

| Assessment          |                    | Blood sample volume (ml) |
|---------------------|--------------------|--------------------------|
| Immunology/Virology |                    | 31                       |
| Safety              | Clinical chemistry | 5                        |
|                     | Haematology        | 14                       |
| Total               |                    | 50                       |

Inclusive of screening evaluations, samples will be collected at 12 different time points throughout the study, resulting in the collection of approximately 460 ml blood over a period of at least 48 weeks. All blood samples will be collected by venipuncture.

General laboratory tests as detailed in section 6.6.2 will be performed at the NHLs Laboratory of the DGM Hospital. Blood samples for these tests will be collected at the Clinical Research Unit and transferred to the laboratory so that the testing procedures begin within three hours of sample collection. Results will be forwarded to the investigator as soon as available, in accordance with test-specific turn-around-times.

Specialised immunological and virological evaluations (as detailed in sections 6.6.3 and 6.6.4) will be performed in part at the NHLs Laboratory and at the designated Core Lab. A Core Laboratory of Immunology and Virology (*Core Laboratory of Immunology and Virology Ospedale S. Gallicano IFO, Rome*) will perform all the immunologic testing to assess the anti-Tat immune response and the virological assessments that go beyond the routine clinical monitoring of the patients.

Blood samples to be transferred to the NHLs and/or to the Core Laboratory for immunologic and virologic investigations will be collected and processed according to the procedures described by the protocol-specific Specimen Management Manual which will be provided to the investigational site prior to study initiation. Thereafter, cryopreserved cellular specimens and sera will be stored in liquid nitrogen or at  $-80^{\circ}\text{C}$  prior to be shipped to the Core Lab of immunology and virology (IFO San Gallicano Hospital, Rome). Shipment to the Core Lab will be done on dry ice, through a specialized courier, within 15 days of the date of sample collection.

Each sample will be identified with the following information: protocol number, centre number, subject screening number (i.e. subject identifier), visit number, sample type (plasma, serum or whole blood) and the sample collection date.

The residual specimens (PBMC, serum or plasma) available after the conduct of the first line tests, will either be used immediately, or kept frozen for later use, for the determination of additional second line tests (refer to sections 6.6.3 and 6.6.4).

As an exploratory test to detect possible HPV infection, cervical swabs and Pap smears will be collected from female participants at 3 time points throughout the study. Samples will be analysed at the S. Orsola Malpighi Hospital (Bologna, Italy).

## 6.7 Schedule of Study Procedures

The schedule of study visits and assessments is as follows:

### Day -35 to -1: Screening Period

Informed consent for the study will be obtained prior to any study specific procedures.

At screening, the following procedures will be performed:

- Signed informed consent
- Medical History (including HIV-specific and TB history);
- Previous and concomitant medication history (including a complete history of all anti-retroviral treatments taken by the subject as far as possible)
- Complete physical examination including height and weight;
- Vital signs after 5 minutes in a resting position (seated blood pressure, heart rate, respiratory rate and axillary body temperature);
- Counselling: Pre- & post-HIV test counselling, ARV adherence, risk reduction and the prevention of pregnancy
- Serum  $\beta$ HCG pregnancy test (for all females)
- Standard haematology, clinical chemistry, coagulation and urinalysis assessments (as described in section 6.6.2 )
- Chest x-ray if an x-ray examination performed within 6 months prior to screening is not available to exclude active or acute cardiac or pulmonary disease, including Pulmonary Tuberculosis.
- Thyroid function tests (T4 & TSH)
- CD4+ T cell
- Virological evaluation: HIV-1/HIV-2 ELISA
- HIV-1 plasma viraemia
- Anti-Tat antibodies (IgM, IgG, IgA)
- Assessment of eligibility as per inclusion and exclusion criteria, and results of all assessments performed.

### DAY 0 (Baseline)

#### Prior to the vaccine administration:

- Physical examination including weight;
- Vital signs after 5 minutes in a resting position (seated blood pressure, heart rate, respiratory rate and axillary body temperature)
- Concomitant medication
- Standard haematology, clinical chemistry, coagulation and urinalysis assessments (as described in section 6.6.2)
- Urine dipstick pregnancy test (for females of child-bearing potential only)
- CD4+ T cell counts
- HIV-1 plasma viraemia
- Anti-Tat antibodies (IgM, IgG, IgA)
- Cervical swab and Pap smear for detection of HPV infection (Female participants only)
- Review of medical history and eligibility criteria (before the first vaccination)
- Immunological & Virological sample collection and storage.

Note: If the subject has a body temperature  $\geq 37.5$  °C or, in the investigator's opinion, an acute illness, **DO NOT VACCINATE**; re-schedule the Day 0 visit.

**Vaccine administration:**

The next available treatment kit (sequential number) at the site will be allocated to the subject as described in section 6.4. The vaccine will be diluted and administered as described in section 5.1.

**Post-vaccination procedures:**

After administration of the investigational product, subjects will remain at the study centre for 2 hours for the following assessments, at 0.5 hours, 1 hour and 2 hours after vaccination respectively:

- Symptom-directed physical examination
- Vital signs after 5 minutes in a resting position (seated blood pressure, heart rate, respiratory rate and axillary body temperature)
- Assessment of adverse events.
- Distribute and review diary card and diary card instructions.

During this period the subject will not consume any food or beverages other than water. Prior to discharge from the clinical facility, subjects will be counselled on ARV adherence, risk reduction and the prevention of pregnancy.

After Day 0 (the first vaccination) the next 2 vaccination visits will be scheduled at 28-day (4 week) intervals. The next visit will be scheduled for 7 days ( $\pm 1$  day) later.

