Assessment of safety was performed at baseline and at several time points during the study. Overall, no clinically significant alterations in laboratory values have been identified in any treatment group. AEs were coded according to the MedDRA dictionary and grouped in accordance to the MedDRA System Organ Classes (SOC). An independent, “ad hoc” safety monitoring board periodically evaluated all safety documentation including the frequency and characteristics of AEs. Safety monitoring confirmed that the vaccine based on the recombinant Tat protein is safe and well tolerated. The most frequent AEs were mild and did not appear to be clearly dose related, including injection site reactions, asthenia, fever, headache and transient blood disorders (mainly leukocytosis and neutrophilia).

Vaccination efficiently induced both humoral and cellular immune responses against the Tat protein (Ensoli et al AIDS 2008 and Vaccine 2009, Longo et al Vaccine 2009, Bellino et al Rev Rec Clin Trials 2009). In particular, in HIV-infected asymptomatic individuals, intradermal vaccination with Tat (given 5 times on a monthly schedule), in the absence of adjuvant, not only induced functional antibodies, but also partially reverted the marked Th1 polarization of anti-Tat immunity seen in natural infection eliciting a more balanced Th1/Th2 immune response (Ensoli et al AIDS 2008, Longo et al Vaccine 2009). Remarkably, the number of CD4+ T cells had a significant positive correlation with anti-Tat antibody titers, which persisted up to 144 weeks after the first vaccination (Ensoli et al Vaccine 2009, Longo et al Vaccine 2009, Bellino et al Rev Rec Clin Trials 2009).

Based on these data, a phase II therapeutic, open label, clinical study with Tat protein (ISS T-002, ClinicalTrials.gov NCT00751595) was sponsored by ISS and activated in 10 clinical sites in Italy in HIV-infected HAART-treated subjects negative for anti-Tat antibodies at baseline, with undetectable viral load and no evidence of virological rebounds (viral <50 copies/ml in the last 6 months before enrolment), with CD4+ T cell counts >400 cells/μl and a CD4 nadir >250 cells/μl. In this study, subjects are randomized into two arms to receive 3 or 5 vaccinations monthly; each arm is composed of two treatment groups, receiving 7, 5 or 30 μg of Tat, respectively.

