#### **9.3.1 Assessing Severity**

The safety concepts of "severity" and "seriousness" are distinct concepts. Severity refers to the degree of clinical manifestation. "Seriousness" refers to pre-defined outcomes from an adverse event. A severe adverse event is not always serious and a serious adverse event is not always severe.

For all adverse events the investigator (or qualified designee) is responsible for assessing the severity of the event and the causal relationship of the event to the study vaccine.

The severity of all adverse events, including clinical findings and abnormal laboratory values, will be classified as one of the following grades:

1. Mild
2. Moderate
3. Severe

A Toxicity Table (adapted for this protocol from the Division of Aids table for grading the severity of Adult and Pediatric Adverse Events Version 1.0, December, 2004; clarification August 2009) is provided as an appendix to the protocol for the assessment of severity of specified adverse events. The Toxicity Table Adverse Event Grades do not correlate directly with the classical severity grades of mild, moderate and severe. **For the purposes of recording events in the CRF** Toxicity Table Grade 1 events will be considered mild in severity, Toxicity Table Grade 2 & 3 events will be considered moderate in severity, and Toxicity Table Grade 4 events will be considered as severe.

For adverse events not listed in the Toxicity Table determination of severity requires some level of interpretation as outlined below. The degree of incapacity caused by the adverse event and the level of medical intervention required for treatment may be helpful in assessing the overall severity of the adverse event.

For example:

- Mild events are generally regarded as noticeable but have no impact on normal activities; they may or may not require over-the-counter treatment managed by the subject.
- Moderate events generally have some impact on an individual's normal activities and may require general symptomatic medical intervention by a healthcare professional or by the subject.
- Severe adverse events may be incapacitating, leading to suspension of normal daily activities, and would generally require more immediate medical evaluation and intervention by a healthcare professional.

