### **9.8 Subject Diary and Temperature Monitoring**

Subjects will receive, and be instructed in, the operation of a daily adverse event diary and a thermometer to be used during the 7-day post-vaccination diary period after vaccine administration. The daily adverse event diary is a source document and will record solicited adverse events, daily thermometer assessments of body temperature, and any other adverse events. At the safety visits scheduled 7 days after each vaccination the diary card will be collected and reviewed by the principal investigator (or designee) at which time any clinical details required for complete understanding of the information recorded will be obtained. Diaries not brought to the scheduled visit should be obtained before adverse event assessment can be performed. Lost diaries will be reconstructed as possible on a new diary booklet by the subject from memory at the closest clinic visit and labeled as a reconstructed diary. Adverse events obtained from the diary will be recorded and completely assessed on the Adverse Event CRF. Body temperatures below 38° C will not be considered fevers.

Any change to an AE recorded by the subject on the diary card (e.g., the severity level of an event is changed after interviewing the subject) based on the investigator's evaluation of the event must be explained by notation in source documentation.

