| Chills                                                                                           | Symptoms causing no or minimal interference with usual social & functional activities | Symptoms causing greater than minimal interference with usual social & functional activities                      | Symptoms causing inability to perform usual social & functional activities                               | NA                                                                                                                                    |
| Fatigue
Malaise                                                                               | Symptoms causing no or minimal interference with usual social & functional activities | Symptoms causing greater than minimal interference with usual social & functional activities                      | Symptoms causing inability to perform usual social & functional activities                               | Incapacitating fatigue/ malaise symptoms causing inability to perform basic self-care functions                                       |
| Fever
(non-axillary)                                                                          | 37.7 – 38.6°C                                                                         | 38.7 – 39.3°C                                                                                                     | 39.4 – 40.5°C                                                                                            | > 40.5°C                                                                                                                              |
| Pain
DO NOT use for pain due to injection (See Injection Site Reactions: Injection site pain) | Pain causing no or minimal interference with usual social & functional activities     | Pain causing greater than minimal interference with usual social & functional activities                          | Pain causing inability to perform usual social & functional activities                                   | Disabling pain causing inability to perform basic self-care functions OR Hospitalization (other than emergency room visit) indicated  |

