2 If no chest x-ray available within 6 months of screening period

3 After 5 minutes in a resting position (seated blood pressure, heart rate, respiratory rate and axillary body temperature)

4 All females

5 Females of child-bearing potential only

6 The same sample of urine to be submitted for microscopy and culture if dipstick results are abnormal and clinically significant

7 Counselling: Pre- and post HIV test at screening, and ARV adherence, risk reduction and prevention of pregnancy at other designated visits

8. Site to contact subject telephonically to give results of the following tests done during Visit 12: haematology, clinical chemistry, coagulation and urinalysis assessments CD4+ T cell counts, HIV-1 plasma viraemia. Pap smear results will be communicated as soon as they become available. Subject will be requested to come to the site if there is a need for a referral to a health facility.

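### Clinic temperatures are axillary but the only fever scale is for non-axillary readings, so fever has no consistent grading route

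*Protocol*

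**What the plan says.** **Clinic readings.** Section 6.7 asks for "Vital signs after 5 minutes in a resting position (seated blood pressure, heart rate, respiratory rate and axillary body temperature" at screening, before each vaccination, at 0.5, 1 and 2 hours afterwards, at the Day 7, 35 and 63 safety visits, and at each later clinic visit. Footnote 3 of Appendix II says the same for the whole schedule: "After 5 minutes in a resting position (seated blood pressure, heart rate, respiratory rate and axillary body temperature".

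**Diary readings.** Section 9.8 collects "daily thermometer assessments of body temperature" for seven days after each vaccination and gives no measuring site. It adds that "Body temperatures below 38° C will not be considered fevers".

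**Grading scale.** The fever row of Appendix I is labelled "Fever (non-axillary". Its bands are 37.7–38.6 °C (Grade 1), 38.7–39.3 °C (Grade 2), 39.4–40.5 °C (Grade 3) and above 40.5 °C (Grade 4). The appendix states that the table was adapted for this protocol.

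**Use of the grade.** Section 9.3.1 states: "The severity of all adverse events, including clinical findings and abnormal laboratory values, will be classified as one of the following grades". The grades are mild, moderate and severe. Grade 1 maps to mild, Grades 2 and 3 to moderate, and Grade 4 to severe. Events that the table does not list are rated by incapacity and the intervention needed. Section 9.2.1 counts a rise in toxicity grade from baseline among adverse events, and section 12.7 tabulates adverse events by severity.

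**Relevance of fever.** Section 2.1 reports from the Phase I trials: "The most frequent AEs were mild and did not appear to be clearly dose related, including injection site reactions, asthenia, fever, headache".

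**The concern.** The protocol measures temperature at one site and grades it on a scale expressly written for other sites. Nothing links the two, and the diary readings carry no site at all. Two assessors with the same axillary reading could properly do different things. One could apply the Appendix I bands; the other could decide that the row does not apply and rate the event by its effect on activities.

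The grade can decide whether a temperature rise counts as an adverse event (9.2.1), and it sets the severity under which the event is tabulated (9.3.1, 12.7). Safety against placebo is the trial's secondary objective, and systemic reactions and vital signs are named secondary endpoints (8.2). An undefined scale for one of the commonest known reactions therefore affects the reported reactogenicity of the vaccine.

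**Working it through.** The plan states no figure on this point, so there is none to reproduce. The check is a comparison of the text, followed by an illustration under an assumed offset.

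**1. The passages side by side**

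| Place | Site | Fever rule |
|---|---|---|
| 6.7 and Appendix II footnote 3 | axillary | none for grading |
| 9.8, diary | not stated | below 38 °C is not a fever |
| Appendix I | non-axillary | graded from 37.7 °C |
| 9.3.1 | none | functional descriptors for events the table does not list |

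Read literally, the Appendix I row covers no temperature taken at a clinic visit. Fever is nevertheless listed in the table, so it is not plain that the 9.3.1 fallback applies either.

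**2. What happens if axillary readings are put on the Appendix I bands**

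Inputs from the document: the lower edges of the four grades, which at 0.1 °C resolution are 37.7, 38.7, 39.4 and 40.6 °C, and the mapping from grade to CRF severity. Assumption, not in the documents: the axillary reading is *d* °C below the non-axillary one, with *d* from 0 to 1.0.

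Take non-axillary temperatures from 37.7 to 41.0 °C in steps of 0.1 °C, which gives 34 values. Grade each value, subtract *d*, and grade again. For *d* up to 0.5 the count is simple:

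- grade changed = 4 lower edges × *d*/0.1;
- CRF severity changed = 3 lower edges × *d*/0.1, because the edge at 39.4 °C lies within moderate;
- reading below 37.7 °C = *d*/0.1.

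At *d* = 0.3 this gives 4 × 3 = 12, 3 × 3 = 9 and 3. At *d* = 1.0 the shift is longer than some bands, so the values were counted directly.

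| Assumed *d* (°C) | Grade changed | CRF severity changed | Below 37.7 °C |
|---|---|---|---|
| 0 | 0 of 34 | 0 of 34 | 0 of 34 |
| 0.3 | 12 of 34 | 9 of 34 | 3 of 34 |
| 0.5 | 20 of 34 | 15 of 34 | 5 of 34 |
| 1.0 | 32 of 34 | 25 of 34 | 10 of 34 |

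These are counts of grid points, not proportions of patients. They show how sensitive the bands are to a shift and do not forecast how many fevers would be misgraded.

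**3. The second inconsistency**

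Readings of 37.7, 37.8 and 37.9 °C are Grade 1 in Appendix I but not fevers under 9.8. This holds for any offset, including zero.

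**The case against.** Several points on the other side are sound.

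- **Fever is not left ungraded.** A reader might infer that it is. Section 9.3.1 requires a severity for every adverse event and supplies a functional route, so the fault is an undefined choice between routes.
- **Grading too low is conditional.** The protocol gives neither the size nor the direction of an axillary offset. At zero offset nothing changes grade. The effect needs both a lower axillary reading and use of the non-axillary bands.
- **The proven mismatch is confined to clinic readings.** Between the 2-hour check and the Day 7 visit, the diary is the scheduled temperature record. Its site is unstated, which is not the same as wrong.
- **No share of missed fevers can be given.** A reader might model febrile temperatures as 37.7 °C plus an exponential with mean 0.6 °C and, with readings rounded to 0.1 °C, obtain 1 − exp(−0.25/0.6) = 34% missed at a 0.3 °C offset and 1 − exp(−0.55/0.6) = 60% at 0.6 °C. Neither the distribution nor the offsets are in the documents, and the result could apply only to clinic readings. At 0.3 °C the missed values lie below 37.95 °C, where 9.8 already says there is no fever.
- **Some grade shifts do not reach the CRF.** Grades 2 and 3 share one severity, hence 9 rather than 12 values at 0.3 °C.
- **No arm is favoured by design.** Both blinded arms use the same procedure, and section 12.7 plans summaries of adverse events, not a fever test.

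These points limit the consequence. They do not remove the contradiction: the table lists fever, excludes the site used at the clinic, and does not say what to do instead.

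**Conclusion.** The contradiction stands on the text alone. Axillary clinic readings have no defined place on the protocol's only fever scale, and diary readings cannot be tied to it. Following the plan means either using a scale that excludes the reading or leaving the route to each assessor.

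The size is conditional. With no offset, no grid value is regraded. If axillary readings are 0.3 to 0.5 °C lower and are placed on the Appendix I bands, 12 to 20 of the 34 grid values change grade and 9 to 15 change CRF severity. What is at risk is the absolute fever rate and its severity in both arms. A difference between arms would be distorted only as a by-product: if the same share of fevers were missed in each arm, the observed difference would shrink by that share. The documents do not support a claim of built-in bias towards Tat or placebo.

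This is a modest defect but worth correcting, because it concerns a frequent known reaction and the remedy is small.

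**What to change.** Reconcile sections 6.7 and 9.8 with Appendix I so that temperatures used for adverse event grading and the fever scale refer to the same site. This can be done in either of two ways:

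- take the readings used for grading at a site the existing row covers; or
- add to Appendix I a row for the site actually used, with cut-offs that the sponsor justifies, since the documents supply none.

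In both cases, state the diary thermometer site in 9.8, add a site field to the CRF and diary, and say in 9.3.1 which route applies to a temperature that the row does not cover. In the same revision, reconcile the 38 °C statement in 9.8 with the Grade 1 band that starts at 37.7 °C. This review takes no position on which threshold is right.

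The pre-vaccination temperature rule in 6.7 should stay as it is. It appears alongside the same axillary vital signs, so changing the site for grading would mean a separate reading on vaccination days. Adding a row avoids that and keeps changes from baseline in vital signs comparable.

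Cost: the wording must be aligned at several visits and in the Appendix II footnote, or one table row added, plus the site field. Somewhat more low-grade fevers may be reported in both arms.
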